## Abstract

**BACKGROUND AND OBJECTIVES::**

There are still major global differences in the treatment of acute traumatic thoracolumbar burst fractures in patients without neurological deficits and without posterior column injury. Treatment strategies range from conservative treatment with orthosis or early functional mobilization to various surgical stabilization techniques. The study's objectives are to evaluate the clinical (Oswestry Disability Index [ODI]) and radiographical outcomes (restoration and maintenance of spinal alignment; injury of the affected intervertebral disk) and determine the prevalence of complications until 24 months of follow-up.

**METHODS::**

The study is designed as a randomized, controlled, noninferiority clinical trial. All patients with a thoracolumbar burst fracture (*Arbeitsgemeinschaft für Osteosynthesefragen* spine type A3 or A4) age 18 to 70 years without neurological deficit and without posterior ligament injury can be enrolled. We will randomly assign 52 patients for either surgical or nonsurgical treatment. The surgical group will receive combined anterior–posterior (360°) spinal stabilization therapy. Participants in the nonsurgical group will be treated with a 3-point hyperextension orthosis for 6 weeks. The primary outcome is the difference in ODI at 2 years after injury.

**EXPECTED OUTCOMES::**

We expect to find that conservative treatment of burst fractures in the thoracolumbar spine will be noninferior to the surgical treatment.

**DISCUSSION::**

This study will provide high-quality data comparing a modern surgical treatment regime with a standardized conservative treatment in patients with thoracolumbar burst fractures.

ABBREVIATIONS:AO
*Arbeitsgemeinschaft für Osteosynthesefragen*
EDCelectronic data capturingODIOswestry Disability Index.

## RATIONALE AND BACKGROUND INFORMATION

Most spinal fractures occur at the thoracolumbar transition zone, which includes the 10th thoracic to the 3rd lumbar vertebra.^1,2^ Spinal fractures are classified according to the *Arbeitsgemeinschaft für Osteosynthesefragen* (AO)-Spine classification of thoracolumbar fractures. This classification system separates 3 major types (A, B, and C) with increasing injury severity based on the involvement of the functional columns (anterior, middle, and posterior), mechanism of injury, and fracture morphology (Figure 1A). Incomplete (AO type A3) and complete burst fractures (AO type A4) are distinguished by the involvement of one or both endplates of the vertebral body (Figure 1B). A high consensus exists that traumatic burst fractures with neurologic deficit, as well as those with disruption of the posterior tension band complex (posterior column), experience better outcomes with surgical treatment compared with nonsurgical (Figure 1C).^3^ However, no treatment recommendation exists for traumatic burst fractures without a neurologic deficit and without the involvement of the posterior column.^3,4^

**FIGURE 1. F1:**
[figure not shown]
**A**, Biomechanical three-column model of the spine published by Denis in 1983. Compression forces on the anterior column result in vertebral body fracture, whereas tension forces on the posterior column led to a ligamentous injury. **B**, Example of a complete (one endplate of the vertebral body injured) vs an incomplete vertebral body fracture (both endplates of the vertebral body fractures). **C**, Decision-making tree for treatment of burst fractures: neurological deficits and posterior column injury are clear indications for surgical treatment. On the contrary, the optimal treatment for neurologically intact patients without a posterior column injury is still unclear. *Created with*
BioRender.com. AO, *Arbeitsgemeinschaft für Osteosynthesefragen*.

We hypothesize that nonsurgical management of thoracolumbar burst fractures will be noninferior to surgical treatment in patients without neurological deficits and without injury of the posterior column.

## STUDY GOALS AND OBJECTIVES

### Primary Goals

To investigate whether nonsurgical treatment with bracing (possibly followed by surgery if there is a deterioration or lack of satisfaction) of an acute traumatic burst fracture of the thoracolumbar region (10th thoracic to 3rd lumbar vertebral body) without injury of the posterior tension band/posterior column and neurological deficits is noninferior to the surgical treatment concerning the clinical outcome.

### Secondary Goals

The secondary objectives of the study are to investigateThe changes in spinal alignment/kyphosis, the grade of intervertebral disk degeneration, and healing rate (nonsurgical group) or spinal fusion rate (surgical group),The patient-reported outcomes of the surgical and nonsurgical treatment groups,The costs comparing surgical vs nonsurgical treatment options,Patients' outcomes on incomplete vs complete burst fractures.

## STUDY DESIGN

This study is designed as an investigator-initiated, multicenter randomized controlled clinical trial. The study protocol complies with the SPIRIT 2013 statement. The selection criteria are presented in Table.

**TABLE. T1:** Selection Criteria

Inclusion criteria	Exclusion criteria
Acute traumatic burst fracture of the thoracolumbar spine (10th thoracic to 3rd lumbar vertebral body)	Injury of the posterior tension band/posterior column of the thoracolumbar spine^5,6^
Age 18-70 y at inclusion	Any neurological deficit (American Spinal Injury Association Impairment Scale Grade A-D)^7^
Informed consent for study participation	Pathological vertebral body fractures (suspected by MRI, computed tomography scan, and patient history)^a^
	Concomitant spinal fractures at any other level of the spine outside the T10-L3 level^a^
	Multiple trauma or Injury Severity Score ≥16 or additional injuries^a^
	Any known previous spinal surgery in the thoracolumbar spine^a^
	Any severe, progressive, or uncontrolled medical or psychiatric condition^a^
	Known history of substance abuse (ie, recreational drugs, alcohol)^a^
	Any severe systemic medical disease that would exclude the patient from being a potential candidate for surgery
	Pregnancy or women planning to conceive within the study period. All women included in this study must have a negative blood pregnancy test (human chorionic gonadotropin blood level at visit 1. If pregnancy occurs during the study period, the patients drop out of the study)
	Inability to follow the procedures of the study, eg, because of inability to understand German, French, or English^a^

a Which, in the opinion of the research/investigative team, would compromise (or interfere with) patients' ability to participate in the study.

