## DATA MANAGEMENT AND STATISTICAL ANALYSIS

Data collection will be performed electronically using a dedicated electronic data capturing (EDC) system (Research Electronic Data Capture). Responsibility for hosting the EDC system and the database lies with CTU Bern.

The primary end point will be Oswestry Disability Index (ODI) change from baseline at 104 weeks. The report assumes that baseline ODI will be 45 and 1-year ODI will be 25 (a difference of 20), as we assume noninferiority, the expected mean difference in both groups is the same.^7,8,14^ Assuming that the difference between baseline and 1-year follow-up is 20 ODI points, the SD of the difference is 6 (based on previously collected data of a prospective trial^15^), and the noninferiority margin is 5.5, 38 participants in total (19 in each arm) would be needed to show noninferiority. By assuming a dropout rate of 20% and a possible crossover from the nonsurgical to the surgical group, we will enroll a total of 52 patients (26 in each arm).

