## DURATION OF THE PROJECT

The planned study duration from the first participant's first visit to the last participant's last visit is 4 years. The planned recruitment period from first participant's first visit to the last participant's first visit is 2 years. The study duration for each participant is 2 years.

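### Dropping a patient from the study when she becomes pregnant gives up a 104-week ODI that could still be collected (minor, cheap to fix)

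*Protocol article*

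**What the plan says.** The Table of selection criteria in the protocol article (Study Design) lists as an exclusion "Pregnancy or women planning to conceive within the study period" and requires a negative blood pregnancy test at visit 1. The same cell adds a rule for later events: "If pregnancy occurs during the study period, the patients drop out of the study". The age criterion is "Age 18-70 y at inclusion", so women of childbearing age can be enrolled.

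Under Duration of the Project, "The study duration for each participant is 2 years". Under Data Management and Statistical Analysis, "The primary end point will be Oswestry Disability Index (ODI) change from baseline at 104 weeks". The Abstract lists ODI as the clinical outcome, separate from the radiographic outcomes, and sets an objective on complications up to 24 months. The Follow-up section plans adverse event collection at the routine visits. Nothing in the article says that ODI or adverse events are still collected after a pregnancy.

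**The concern.** Excluding pregnancy at entry shapes the population before randomisation and is not at issue. The added sentence is different: it ends participation because of something that happens after randomisation, possibly many months later. It refers to the study as a whole, not to a particular procedure or to imaging.

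At stake is the patient's 104-week ODI, together with her adverse event data and other patient-reported outcomes from that point on. An analysis plan can decide how to handle a missing value, but it cannot recover one that was never collected. The Primary Goals section compares strategies, with bracing possibly followed by surgery. A comparison of that kind is best served by following every randomised patient to the endpoint. In a trial of 52, a loss written into the protocol should have a reason, and none is given.

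**Working it through.** **1. Does the rule reach the primary endpoint?** The trigger is pregnancy during the study period. Each participant is in the study for 2 years and the primary ODI is due at 104 weeks. A pregnancy at any point after randomisation therefore leads to dropout before, or at, the primary assessment.

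**2. Does the article give a reason why the ODI could not be collected?** No. ODI is listed apart from the radiographic outcomes, and no section ties its collection to imaging or to a procedure.

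**3. Reproducing the plan's sample size.** Inputs from Data Management and Statistical Analysis: "the SD of the difference is 6", "the noninferiority margin is 5.5", and a true difference of zero ("as we assume noninferiority, the expected mean difference in both groups is the same"). Alpha and power are not stated; one-sided 0.025 and 80% are assumed.

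n per arm = 2 × (1.960 + 0.842)² × 6² / 5.5² = 2 × 7.85 × 36 / 30.25 ≈ 18.7, rounded up to 19, or 38 in total. This matches the article.

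**4. The dropout allowance.** 19 / 0.80 = 23.75, rounded up to 24 per arm, or 48 in total. The article enrols 52; the remaining 4 fit its stated but unquantified allowance for crossover. At 52 enrolled, 20% dropout is 10.4 patients, leaving 41.6 evaluable. A pregnancy withdrawal is itself a dropout, so it may be one of those 10.4.

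**5. Cost of losses beyond the 20%.** The documents give no pregnancy rate, so 0 to 3 extra losses are assumed. Power is from the noncentral t distribution with N evaluable patients split equally, df = N − 2 and noncentrality 5.5 / (6 × √(4/N)), at one-sided 0.025.

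| Extra losses | N evaluable | Noncentrality | Power |
|---|---|---|---|
| 0 | 41.6 | 2.96 | 82.2% |
| 1 | 40.6 | 2.92 | 81.3% |
| 2 | 39.6 | 2.88 | 80.2% |
| 3 | 38.6 | 2.85 | 79.2% |

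The cost is about one point of power per patient, and two extra losses still leave power above 80%. The t-based figures run slightly below the normal approximation that reproduces 38: at 19 per arm the two give 78.5% and 80.7%.

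**6. Effect of the fix on sample size.** None: 38 evaluable and 52 enrolled stay as they are.

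**The case against.** The case against has several parts, and much of it stands.

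- **Frequency.** Women planning to conceive are excluded, a negative test is required at visit 1, and the 52 patients are of both sexes up to age 70. The number may well be zero. This stands and is the main reason the point is minor.
- **Double counting.** A reader might subtract the full 20% dropout, compare 41.6 with 38, and conclude that each pregnancy uses 1 / 3.6 = 28% of the reserve. The documents do not support this. Pregnancy withdrawals belong to the dropout already budgeted, and the patients left over also have to cover crossover.
- **Treatment not always complete.** One might infer that the allocated treatment has always been given by the time of a pregnancy. It has not: the surgical arm has a CT at 6 months and implant removal at 6 to 9 months, and later surgery is part of the nonsurgical strategy. A pregnancy may interfere with these procedures. That does not show that an ODI cannot be collected.
- **ODI may be affected.** Pregnancy-related back pain could enter the score. This is a reason to flag such values, not to leave them uncollected.
- **The randomised comparison.** One might infer that the rule breaks it. The article does not go that far: it ends participation but does not remove the patient from the analysis or discard ODI already recorded. Analysis sets and missing-data methods may properly be set out in an analysis plan that is not shown.
- **Bias.** One can construct a large figure: three losses in one arm of 26, each with an ODI change differing by 20 points, shift that arm's mean by 3 × 20 / 26 = 2.31 points, or 42% of the 5.5 margin. The number, the allocation to one arm and the 20 points are all assumed. The documents also contain nothing on whether conception is related to recovery.
- **Condensed article.** The full protocol may provide for follow-up after withdrawal. That cannot be excluded, but the published sentence is an explicit rule that says otherwise.

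**Conclusion.** The point holds as an avoidable loss of primary outcome and adverse event data, caused by an explicit rule that acts after randomisation. Its severity is minor. The expected number is unknown and probably small (0 to 3 is an assumption), the losses may already be covered by the 20% dropout allowance, and any beyond it cost about one point of power each. Those power figures rest on SD 6, margin 5.5, no true difference, and an assumed one-sided alpha of 0.025. No sample-size figure in the article is wrong because of the rule, and the documents do not establish a bias in either direction. The case for changing it is that the data can be kept at almost no cost.

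**What to change.** Keep pregnancy at entry as an exclusion. Reword the later sentence so that stopping study procedures is separate from leaving follow-up: where the patient agrees, ODI, other patient-reported outcomes and adverse events are collected to 104 weeks. State that she is analysed in her randomised arm, with a sensitivity analysis that flags ODI values taken during pregnancy. Imaging and clinical management in pregnancy are for the sponsor to decide. If the full protocol already provides for this follow-up, the two texts should be brought into line.

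The cost is a one-sentence amendment, with no change to sample size. Trial Status says enrolment is ongoing, so the change can still preserve data. The downsides are that some radiographs will be missing for these patients, and that an ODI taken in late pregnancy may include pregnancy-related back pain.

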## METHODOLOGY

### Study Setting

The study is conducted in Switzerland. The study site is the Inselspital, University Hospital Bern, which is a level 1 trauma center. The other sites are the Spine Center of Eastern Switzerland, Cantonal Hospital St. Gallen, and Department of Traumatology, University Hospital Zurich, Zurich, Switzerland. The addition of more study sites will depend on the enrollment status. The selection criteria are presented in Table. Flowchart is shown in Figure 2.

**FIGURE 2. F2:**
[figure not shown]
Study flowchart. CT, computer tomography; ED, emergency department; REDCap, research electronic data capture; XR, x-ray. Created with Biorender.com.

### Interventions

#### Surgical Treatment Protocol: Anterior–Posterior Stabilization With an Expandable Cage

Surgical treatment will be performed under general anesthesia. With the patient in a prone position, the surgeon will perform a minimally invasive (percutaneous) posterior stabilization of the injured spinal segments (Figure 3A and 3B). In a second stage procedure performed on the same day or separately, a (partial) corpectomy will be performed (Figure 3C). Immediately after surgery, the patient can start mobilization. After the hospitalization, weekly physiotherapy visits are prescribed. In the first 6 weeks, the rehabilitation program includes isometric training, activation, and circulation promotion. After 6 weeks, range-of-motion exercises can be added. Spinal fusion will be confirmed by a computed tomography scan 6 months after the index procedure before the removal of the posterior implants (pedicle screw/rod system).

#### Nonsurgical Treatment Protocol

All patients will receive external bracing (3-point hyperextension brace) for 6 weeks, which must always be worn except when lying flat in bed. After hospital admission, bed rest is prescribed until an experienced orthopedist adjusts the brace. Also, a physiotherapist will instruct the patient to accomplish daily activities with the restriction he or she will have by wearing the brace. Discharge is possible if the patient feels comfortable with the brace and mobilization as well as if adequate pain management has been achieved. After discharge, weekly physiotherapy sessions commence in the week after injury. Initially, the rehab program encompasses isometric exercises, activation routines, and methods to enhance circulation for the first 6 weeks. Subsequently, exercises aimed at improving range of motion are introduced after this period.

## DISCUSSION

To date, only 2 randomized controlled trials have been published comparing surgical vs nonsurgical treatment for traumatic burst fractures.^5,8^ In the study by Wood et al, superior clinical, functional, and equivalent radiographic outcomes were evident after nonsurgical treatment. By contrast, the study by Siebenga et al reported improved clinical, functional, and radiographic results with surgical treatment.^5,8,9^ Particularly, the study by Wood et al, favoring conservative treatment, was limited by a lack of standardization of the treatment protocols. In the surgical group, different and nowadays obsolete surgical techniques and implants were used. Nonsurgical treatment consisted of body casting for up to 12 weeks and additional bracing for another 4 to 8 weeks, resulting in an overall treatment duration of almost half a year.

In the realm of burst fracture treatment, AOSpine spearheaded a prospective multicenter clinical trial focused on this issue.^10^ Moreover, the StUdy oN Burst Fractures (SUNBURST),^11^ a current randomized controlled, registry-based trial, is underway. However, this trial is characterized by variability in surgical treatment across different centers.

To our knowledge, this study is pioneering in comparing nonsurgical with surgical treatment modalities incorporating a standardized 360° stabilization technique for the spine.

## TRIAL STATUS

Enrollment for this study is currently ongoing.

## SAFETY CONSIDERATIONS

Safety assessments will be conducted through physical examinations, analysis of radiographic imaging, and the documentation of any adverse events, including serious adverse events. If there will be a clinical indication (spinal instability measured by a kyphosis >30° on x-ray,^12,13^ intolerable pain, and delayed onset of neurological symptoms) or if the patient is not satisfied after treatment, surgery (anteroposterior stabilization) will be recommended.

### Harms

A causality assessment of the event to the trial intervention (based on the terms given in the International Council on Harmonisation-E2A with modifications) will be done. Any event assessed as possibly, probably, or definitely related is classified as related to the trial intervention. We will make a severity assessment of the event according to the terminology of the Common Terminology Criteria for Adverse Events, version 5.0.^6^ All serious adverse events are documented and reported immediately (within a maximum of 24 hours) to the sponsor-investigator.

## FOLLOW-UP

Patients will be seen on arrival at the emergency department/outpatient clinic to obtain relevant medical history and adverse event collection. After obtaining signed informed consent, patients will be randomly assigned to 1 of the 2 treatment arms. If randomization is refused, the patient will be asked to participate in the observational arm, which is then treated as the current standard operating procedure at our hospital (surgical treatment). After discharge, conservatively treated patients will be seen for an additional visit in the outpatient clinic for 2 weeks (±5 days). Afterward, all participants will have routine follow-up at 6 weeks (±7 days), 13 weeks (±14 days), and 26 weeks (±30 days) after discharge to obtain radiographic images, clinical examination, and adverse event collection. Surgical-treated patients will undergo removal of the posterior instrumentation after 6 to 9 months. Patients will then be seen for follow-up after 1 (±30 days) and 2 years (±45 days) (**Supplemental Digital Content 1**, http://links.lww.com/NS9/A14).

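### The 6-, 13- and 26-week visits are timed from discharge, a post-randomisation event that depends on treatment, and the plan has no common time origin for its visits and primary endpoint

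*Protocol article*

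**What the plan says.** The article uses more than one clock.

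- **Early visits (Follow-up).** Discharge is the origin for three visits in both arms. Two are due at week 6 (a week either side) and week 13 (two weeks either side); the third is set at "26 weeks (±30 days) after discharge to obtain radiographic images, clinical examination, and adverse event collection". The brace arm alone also has an earlier post-discharge visit: "conservatively treated patients will be seen for an additional visit in the outpatient clinic for 2 weeks".
- **Late visits (Follow-up).** "Patients will then be seen for follow-up after 1 (±30 days) and 2 years (±45 days"). The sentence names no origin.
- **Primary outcome (abstract, Methods).** "The primary outcome is the difference in ODI at 2 years after injury". The origin is injury.
- **Primary endpoint (Data Management and Statistical Analysis).** "The primary end point will be Oswestry Disability Index (ODI) change from baseline at 104 weeks". Week 0 is not defined.
- **Randomisation (Follow-up).** "After obtaining signed informed consent, patients will be randomly assigned to 1 of the 2 treatment arms". This takes place around the initial hospital contact, so before discharge.

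What leads to discharge differs by arm. Under the Nonsurgical Treatment Protocol, a patient may leave once at ease in the fitted brace, mobile and with pain under control. Under the Surgical Treatment Protocol, posterior stabilisation is followed by a corpectomy: "In a second stage procedure performed on the same day or separately".

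**The concern.** A visit clock should start at an event that the assigned treatment cannot influence. Discharge does not meet that condition: it comes after randomisation, and its timing reflects brace fitting and comfort in one arm and one or two operations in the other. If one arm stays longer in hospital, all of its discharge-timed visits fall later after injury. The arms are then compared at the same nominal visit but at different stages of recovery.

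At stake are the early between-arm comparisons. The Follow-up section assigns imaging, clinical examination and adverse events to these visits, and they feed the alignment and complication objectives. The 6-week visit is the most exposed: it is the shortest shared interval, and bracing ends and range-of-motion exercise begins at about that time.

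Discharge may also not be a single date. The article does not say whether a separate second stage belongs to the same admission, nor which discharge counts for a brace patient who later has surgery.

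**Working it through.** **The plan's own figure.** The sample size does not depend on visit timing; it is reproduced only to show that the fix leaves it alone. With margin 5.5, SD 6 and true difference 0 (all from the article), and one-sided alpha 0.025 with 80% power (assumed, since the article states neither):

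n per arm = 2 × (1.96 + 0.84)² × 6² / 5.5² ≈ 18.7, rounded up to 19, or 38 in total, as stated. Allowing for 20% dropout, 38 / 0.80 = 47.5, so 48; the article attributes the enrolled total of 52 to dropout together with possible crossover.

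**The timing shift.** Let D be the time from injury to discharge and V the nominal visit time. A discharge-timed visit takes place at D + V after injury, so the between-arm difference in time since injury is

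(D₁ + V) − (D₂ + V) = D₁ − D₂.

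This is the same number of days at every visit, so it weighs most at the shortest interval. If visits are timed from randomisation, D is replaced by the time from injury to randomisation, which is fixed before allocation and balanced between arms in expectation.

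**Size.** D₁ − D₂ is not in the article. For assumed gaps, the shift as a percentage of the nominal interval (gap / interval in days), with gap / window half-width in brackets, is:

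| Assumed gap | 6 weeks (42 days, ±7) | 13 weeks (91 days, ±14) | 26 weeks (182 days, ±30) | 104 weeks (728 days, ±45), if also timed from discharge |
|---|---|---|---|---|
| 3 days | 7.1% (0.43) | 3.3% (0.21) | 1.6% (0.10) | 0.4% (0.07) |
| 7 days | 16.7% (1.00) | 7.7% (0.50) | 3.8% (0.23) | 1.0% (0.16) |
| 14 days | 33.3% (2.00) | 15.4% (1.00) | 7.7% (0.47) | 1.9% (0.31) |
| 21 days | 50.0% (3.00) | 23.1% (1.50) | 11.5% (0.70) | 2.9% (0.47) |

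The windows do not absorb this. They allow individual scatter around the due date, whereas a different origin moves the due date of a whole arm.

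**Would it matter at 2 years?** Take the plan's course from ODI 45 to 25 and assume exponential recovery with a half-life of 6 or 13 weeks:

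ODI(t) = 25 + 20 × 2^(−t / half-life).

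Even if the 2-year visit were timed from discharge, a gap of 3 to 21 days would change ODI at 104 weeks by at most 0.01 points. A straight-line fall of 20 points per year, still running at year 2, gives 20/364 × 3 = 0.16 to 20/364 × 21 = 1.15 points. That deliberately overstates the effect, because the plan has the 20 points reached by 1 year.

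**The case against.** The strongest reply is that nothing here is shown to touch the primary comparison. That stands. A reader might infer that the arms will be compared on the primary endpoint at different times since injury. The article does not support this: the discharge wording covers the visits up to 26 weeks, and the sentence on the 1- and 2-year visits does not repeat it. Even on that reading, the shift lies well inside the ±45-day window.

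A second reply is that the gap is assumed. This also stands. No length of stay is given for either arm. The Nonsurgical Treatment Protocol places the start of outpatient physiotherapy in the week after injury, which hints at early discharge in that arm, but there is no surgical counterpart to set against it. It cannot be said that early results are biased, or towards which arm.

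Two further inferences go too far:

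- **Measuring an early ODI shift against the 5.5-point margin.** That margin belongs to the 104-week endpoint, no noninferiority test is stated at 6 or 13 weeks, and ODI is not listed among the assessments at those visits.
- **Reading the brace-only 2-week visit as biased detection of complications.** Serious events are reported within 24 hours whatever the visit schedule, both arms have weekly physiotherapy, and the surgical arm has contacts of its own (the 6-month CT, implant removal at 6 to 9 months). Net surveillance cannot be ranked from the article.

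Finally, the full protocol and the supplemental schedule are not shown and may name an origin for the late visits. That weakens any complaint about the missing origin taken alone. It does not remove the explicit discharge rule, which would still need reconciling with a schedule counted from another date.

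**Conclusion.** The point holds for the early visits. The article sets a rule that times the 6-, 13- and 26-week assessments from an event which follows randomisation and depends on treatment, and it uses a different origin (injury) for the primary outcome in the abstract. Whether this produces a real imbalance depends on a between-arm difference in length of stay that the article does not give. Under assumed gaps of 3 to 21 days the shift is material at 6 weeks, smaller at 13 weeks, modest at 26 weeks and negligible for the 2-year endpoint. Sample size and the noninferiority conclusion are unaffected. Severity: minor.

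**What to change.** In Follow-up, replace the discharge origin with one common origin for every visit and window in both arms, including the 1- and 2-year visits. The date of randomisation is the natural choice; the date of injury would also serve and would match the abstract. Define the 104-week endpoint from the same date, and align the abstract, Follow-up and statistics sections with it. For patients already enrolled, keep booked visits and use actual time since randomisation when analysing early outcomes.

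The cost is a change to the visit-date calculation in the data capture system. No extra visits or patients are needed, and the totals of 38 evaluable and 52 enrolled stand. Data from the brace-only 2-week visit should stay in the complication comparison, since leaving them out could discard real events.
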